## Methods and analysis

### Study design

This study is a cluster-randomized crossover, multicenter exploratory trial that is designed to assess the safety and efficacy of multiple intervention measures for preventing VTE among perioperative orthopedic trauma patients. The unit of randomization is the orthopedic wards, and each ward will define a cluster, as the proposed interventions are designed to be implemented in all orthopedic wards rather than in selected individual subjects. The study will be conducted at four hospitals in Shanghai from December 2019 through December 2023, including (1) Shanghai Sixth People’s Hospital, Shanghai Jiao Tong University School of Medicine; (2) Jinshan Branch of Shanghai Sixth People’s Hospital, Shanghai Jiao Tong University School of Medicine; (3) Lingang Compound of Shanghai Sixth People’s Hospital, Shanghai Jiao Tong University School of Medicine; and (4) Shanghai Tenth People’s Hospital, Tongji University. A total of five clusters will be determined in the study, according to the routine amount of orthopedic trauma patients visited in those hospitals.

### Inclusion criteria

Perioperative orthopedic trauma patients are considered eligible when they meet the following criteria: aged ≥ 18 years with stable vital signs, Caprini score > 2, and no contraindication of anticoagulation or IPC devices during the study period. Furthermore, patients will be excluded when they have severe open injury in lower limbs which cannot tolerate ultrasonography, venous thromboembolism at enrollment, hepatic and/or renal dysfunctions, and hemorrhage or high risk of hemorrhage in the closed cavity. Female patients in pregnancy or lactation will be excluded as well.

### Interventions

A total of four intervention measures and one control measure will be implemented as follows.

Intervention 1: Fraxiparine (Glaxo Smith Kline, England) nadroparin calcium will be given once a day subcutaneously, with the dosage of 100 Axa IU/kg taking patient’s body weight into account.

Intervention 2: Clexane (Sanofi, France) enoxaparin sodium will be given once a day subcutaneously, with the dosage of 100 Axa IU/kg taking patient’s body weight into account.

Intervention 3: Fraxiparine (Glaxo Smith Kline, England) nadroparin calcium will be given once a day subcutaneously, with the dosage of 100 Axa IU/kg taking patient’s body weight into account. In addition, IPC (Wonjin Mulsan, China) will be administered twice a day, 20 min each time.

Intervention 4: Clexane (Sanofi, France) enoxaparin sodium will be given once a day subcutaneously, with the dosage of 100 Axa IU/kg taking patient’s body weight into account. In addition, IPC (Wonjin Mulsan, China) will be administered twice a day, 20 min each time.

Control: There is no predetermined intervention. The prophylaxis measure against VTE will be administered based on the orthopedists’ decision for the best of patients. The details of the measures will be recorded.

These intervention measures and control measure will alternate along with calendar months (Fig. 1), which means orthopedic trauma patients enrolled in the study will be administered with same measures per cluster per calendar month.

**Fig. 1 Fig1:**
[figure not shown]
Diagram of the study design. Four diverse intervention measures and one control measure were presented based on ten hypothetical periods of 10 months per cluster

### Proposed sample size

We determined the sample size based on the cumulative incidence of VTE. It is estimated that at least 398 orthopedic trauma patients need to be enrolled in each of the five clusters to achieve a power value of 85% to detect an absolute difference of 10% in the cumulative incidence of VTE between the patients with intervention measures and those with control measures (assuming a VTE incidence of 15% according to our retrospective cohort study [5]) at a two-sided alpha level of 0.05. Consequently, approximately 40 patients will be enrolled per intervention measure/control measure per calendar month in each cluster, totaling 1990 patients. The intraclass correlation coefficient (ICC) was calculated based on two levels, 0.228 for patients within the same cluster/time period and 0.15 for patients within the same cluster/different time periods. Due to the lack of data on ICCs related to the current study design and primary outcome, we chose to use a conservative ICC value in our sample size estimation. Moreover, considering a 20% loss of participants, we determine to enroll a total of 2490 patients in the trial, with 498 in each cluster.

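### The 85% power is not tied to a contrast: on the stated ICCs and about 40 patients per ward-month it fits at best four measures pooled against control, while each single measure has about 67–68%

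*Protocol article*

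**What the plan says.** The Proposed sample size section of the protocol article states that "at least 398 orthopedic trauma patients need to be enrolled in each of the five clusters to achieve a power value of 85" per cent. The target is "to detect an absolute difference of 10% in the cumulative incidence of VTE" "between the patients with intervention measures and those with control measures", "at a two-sided alpha level of 0.05". An incidence of 15% is assumed, without naming the arm. The same section plans that "approximately 40 patients will be enrolled per intervention measure/control measure per calendar month in each cluster, totaling 1990 patients". The ICCs are "0.228 for patients within the same cluster/time period and 0.15 for patients within the same cluster/different time periods", and the authors add that, lacking data, "we chose to use a conservative ICC value in our sample size estimation".

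Elsewhere, the Interventions section gives every enrolled patient in a ward the same measure within a calendar month. The Fig. 1 caption shows ten hypothetical monthly periods per cluster. The Hypothesis section concerns LMWH combined with IPC. Statistical analysis principles promises an adjustment for multiple comparisons among interventions, and Primary analysis compares interventions by GEE. The article describes no analysis that merges all four measures against control.

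**The concern.** There are four active measures and one control, so 85% could belong to a pooled contrast or to each measure against control, and these differ greatly in power. The sample size sentence can be read as the pooled contrast. The described analyses and the hypothesis point to comparisons between specific measures. A reader who applies the 85% to a single measure would take a null result as fairly strong evidence against a 10-point effect, when on the plan's own inputs the chance of missing that effect is about one in three.

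The label conservative adds to this. In a crossover the between-period ICC enters with a minus sign, so a high value is the favourable choice, not the cautious one.

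**Working it through.** **Inputs.** From Proposed sample size: two-sided 0.05, 85% power, 10-point difference, 15% incidence, ICCs 0.228 and 0.15, about 40 per ward-month, 398 per ward in five wards (1990). Assumptions: 15% is the control rate (so 15% v 5%), and months are balanced over measures, so that 1990 / 5 = 398 is also the number per measure. The article names no formula; the usual cluster-crossover design effect is used.

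**Design effect.** DE = 1 + (m − 1) × 0.228 − m × 0.15. With m = 40: 1 + 8.892 − 6.000 = 3.892. Effective size per measure: 398 / 3.892 = 102.3.

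**Can the plan's 398 be reproduced?** Yes, for the pooled 4:1 contrast with a continuity correction:
- Uncorrected control n at 15% v 5%: 89.5.
- Corrected: (89.5 / 4) × [1 + √(1 + 2.5 / (89.5 × 0.10))]² = 101.6, rounded up to 102.
- 102 × 3.892 = 397; power at 398 is 85.2%.

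The article states neither the ratio nor the correction, so this route is inferred. A match does not identify the method: 25% v 15% at 1:1 with 8 patients per ward-month also lands there (286 × 1.396 = 399).

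**Pooled 4:1 in other variance forms.**
- Unpooled: SE = √(0.1275/102.3 + 0.0475/409) = 0.0369; 0.10/0.0369 − 1.96 = 0.75; power 77%.
- Average variance: SE = √[0.0875 × (1/102.3 + 1/409)] = 0.0327; power 86%.
- Pooled variance under the null (mean rate 0.07): SE₀ = 0.0282; (0.10 − 1.96 × 0.0282)/0.0369 = 1.21; power 89%.

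**One measure v control (1:1).**
- Unpooled: SE = √(0.175/102.3) = 0.0414; 0.10/0.0414 − 1.96 = 0.46; power 68%.
- Pooled variance: SE₀ = √(2 × 0.10 × 0.90/102.3) = 0.0420; (0.10 − 1.96 × 0.0420)/0.0414 = 0.43; power 67%.
- Needed for 85%: 157.1 × 3.892 = 611 (unpooled) or 160.1 × 3.892 = 623 (pooled variance) per measure, against 398.
- Other treatments at 40 per ward-month: continuity-corrected 58%; arcsine 69%; generalised least squares with period effects 57%; a simulated ward-month linear model with variance pooled over all arms 77%. None reaches 85%.

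**Interventions 3 and 4 pooled v control (2:1).** Unpooled: SE = √(0.1275/102.3 + 0.0475/204.5) = 0.0385; power 74%. Pooled variance: SE₀ = 0.0335; power 81%.

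**Multiplicity.** Bonferroni over four comparisons is an assumption; alpha 0.0125 has critical value 2.50. Single-measure power is then 45–47%.

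**If 15% is the intervention rate (25% v 15%).** Single measure: SE = √(0.315/102.3) = 0.0555; power 43–44%. Pooled 4:1: 58–66%.

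**Sensitivity, one measure v control, 15% v 5%, unpooled.**

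| Patients per ward-month | Between-period ICC | DE | Effective n | Power |
|---|---|---|---|---|
| 40 | 0.114 (half of 0.228) | 5.332 | 74.6 | 54% |
| 40 | 0.15 | 3.892 | 102.3 | 68% |
| 40 | 0.20 | 1.892 | 210.4 | 93% |
| 20 | 0.15 | 2.332 | 170.7 | 88% |
| 10 | 0.15 | 1.552 | 256.4 | 97% |

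Power rises steeply as the between-period ICC rises, so a high value for it flatters the design.

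**The case against.** A reader might infer that 85% cannot follow from the plan's own inputs, or that the trial is shown to be underpowered. The documents do not support either reading. Taken literally, the sample size sentence sets intervention patients against control patients, which fits a 4:1 pooled contrast, and that contrast gives 77–89%, on both sides of 85%. The 1:1 reading is no more explicit in that sentence than the 4:1 reading.

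The single-measure figure also depends on 40 patients per ward-month. The ten periods are called hypothetical, each ward receives several sequences of periods, and recruitment was planned from December 2019 to December 2023. If ward-months turn out smaller, single-measure power reaches about 88% at 20 patients and 97% at 10. In addition, the text speaks of one conservative value, which may mean only the within-period 0.228. The trial calls itself exploratory, and a condensed article may leave the formula and allocation ratio to the full protocol.

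All of this stands against the stronger reading. It does not settle which contrast the 85% covers. A pooled contrast mixes arms with and without IPC, so it cannot isolate the LMWH-plus-IPC combination named in the hypothesis. For the comparisons the article does describe, power at its own 40 per ward-month is below 85%.

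**Conclusion.** The concern holds in a limited form. The article attaches 85% to an unnamed contrast. On its stated ICCs and about 40 patients per ward-month, 85% is attainable only for all four measures pooled against control, and only under some variance forms. A single measure against control has about 67–68%, and the two IPC measures together about 74–81%, before any multiplicity adjustment.

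These figures rest on 15% as the control rate, balanced months, the usual cluster-crossover design effect and 40 patients per ward-month; a change in any of these moves them. The label conservative is wrong if applied to the between-period ICC. Confidence is medium. The point should be corrected, but it falls short of a must-fix, because the stated figure has a plausible derivation and the correction changes neither enrolment nor analysis.

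**What to change.** In Proposed sample size:
- State which contrast the 85% refers to and which arm has the 15%.
- Report single-measure power (about 67–68% at 40 per ward-month) beside any pooled figure, with the formula and design effect, and say whether alpha is adjusted.
- Tie both figures to the actual number of ward-months and patients per ward-month.
- Show a range of between-period ICCs, for example 0.11 to 0.20.
- Limit the word conservative to the within-period ICC.

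The cost is a recalculation and one paragraph, with a less favourable power for single measures if ward-months are near 40. No patients are added.

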### Randomization and allocation

In this study, five clusters will equally share the proposed sample size. In the implementation, each cluster receives several sequences of intervention periods (including four diverse intervention measures) and control periods, which is determined by a randomization, to achieve the allocated sample size (Fig. 1).

Additionally, orthopedic trauma patients are randomly included in these clusters, which might result in a slightly different number of enrolled participants over the periods across the clusters. Thus, we define the duration of a calendar month for each intervention or control period in these clusters, which may ensure the clusters achieve the sample size within the identical number of sequences.

### Data collection

In this study, the primary outcome is the incidence of VTE, which will be measured by trained orthopedists using ultrasound examination (Mindray M8, 8.0–11.0 MHz, China) [17]. Additionally, adverse events following the administration of LWMH and/or IPC will also be recorded and judged by experienced orthopedists, pharmacists, and intensivists, to assess the safety of multiple intervention measures.

The secondary outcomes include the amount of bleeding during operation and mortality within 30 days. Related data will be collected through the hospital information system (HIS) using a standardized case report form (CRF) and recorded using EpiData 4.2. Participants will be followed up from study enrollment to hospital discharge, 30 days after discharge.

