### Quality assurance and data management

Multiple measures will be taken to optimize the implementation of the research activities and ensure the quality of collected data. Before the study initiation, an investigator meeting will be organized, including the principal investigator, orthopedists and senior nurses from the participating orthopedic wards, statisticians, and research assistants. During the meeting, investigators will receive training about study design, implementation plan, and data collection and analysis for all intervention measures. In each orthopedic ward, an experienced staff (A) will be selected and trained about the key aspects of implementation details and further be responsible for monitoring and evaluation. Moreover, all the orthopedic wards will have a learning period within the first 10 days of interventions. Additionally, the measurements used in the study, such as the Caprini score, trauma index score, and VTE assessment, will be recorded [18]. EpiData 4.2 will be used to collect the trial data. In each ward, a trained staff (B) will collect data from HIS using standard CRF. Data cleansing will be conducted by another trained staff (C) every week to ensure the data check and management.

The SPIRIT reporting guidelines were used to ensure the completion of the study protocol (Additional file 1) [19].

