### Data analysis

#### Statistical analysis principles

We will generally perform the analysis using the intention-to-treat (ITT) at the subject level for each outcome. All the participants with a recorded outcome will be included in the analysis according to the intervention group to which they have been randomized. Additionally, we will take the cluster-randomized crossover design effect into consideration. Adjustment for multiple comparisons among interventions will be used. The SAS 9.4 software will be used for all statistical analyses.

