#### Handling of missing data

The least data missing will be expected. All-important observations will be collected and assessed by trained investigators. At the cluster level, orthopedic wards with incomplete patient recruitment will be included in the primary analysis of study outcomes, considering all participants available in each cluster. To assess the risk of bias related to orthopedic wards that have not completed patient recruitment, multiple imputations will be performed for the primary outcome and presented as sensitivity analyses. At the subject level, when a variable is missing, we will assume that most likely the missing variable has a normal or mean value.

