### Secondary analysis

For the secondary outcomes, the amount of bleeding during operation and mortality within 30 days will be presented as mean (or median) difference and 95% CI. GEE will be deployed to compare the difference among interventions or clusters. All the analyses will adjust cluster effect, period effect, and interaction among interventions and periods if applicable.

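### Thirty-day mortality has only the hospital information system as its named source, so deaths outside the hospital may go unrecorded and unknown status can be counted as alive

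*Protocol article*

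**What the plan says.** The Data collection section names two secondary outcomes: "The secondary outcomes include the amount of bleeding during operation and mortality within 30 days". The next sentence gives their source: "Related data will be collected through the hospital information system (HIS) using a standardized case report form (CRF) and recorded using EpiData 4.2". The one after that sets the observation window: "Participants will be followed up from study enrollment to hospital discharge, 30 days after discharge".

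Quality assurance and data management repeats the source and says who does the work: "In each ward, a trained staff (B) will collect data from HIS using standard CRF". The text names no telephone call, clinic visit, family contact or death register as a source of vital status.

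Two analysis rules decide what happens when status is not known. Under Statistical analysis principles: "All the participants with a recorded outcome will be included in the analysis according to the intervention group to which they have been randomized". Under Handling of missing data: "At the subject level, when a variable is missing, we will assume that most likely the missing variable has a normal or mean value".

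**The concern.** A hospital record suits operative blood loss, which occurs in the hospital. It is a less obvious source for deaths up to day 30, some of which may occur at home, in another hospital or in rehabilitation care. The article promises information from after discharge, yet the only source it names is a hospital record abstracted by ward staff. This is therefore more than an omitted contact method: a source is stated, twice, and it fits one of its two outcomes poorly.

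The missing-data rule adds to the problem. For a yes/no death variable, a normal value is most naturally read as alive. A patient whose status nobody checked could then enter the analysis as a survivor.

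Mortality is one of only two secondary outcomes in a trial meant to assess safety as well as efficacy. An undercount would make all five measures look safer than they are.

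**Working it through.** **1. Is there a figure to reproduce?** Not on mortality. The article gives no expected 30-day mortality, length of stay or share of deaths after discharge, and it does not say when the 30 days start. The nearest figure is the loss allowance under Proposed sample size: "considering a 20% loss of participants, we determine to enroll a total of 2490 patients in the trial, with 498 in each cluster". It reproduces: 398 / (1 − 0.20) = 497.5, rounded up to 498; 498 × 5 = 2490; 2490 − 1990 = 500 patients allowed for as lost. The allowance is not specific to mortality and does not measure unknown vital status. It does show that the plan expects incomplete outcomes.

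**2. What the rules do with one patient.** Take a patient discharged before day 30 who has no later entry. The text permits three readings:

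- No death entry is taken as alive. A death elsewhere becomes a survival.
- Status is treated as missing and filled in. A normal value gives alive, as above. A mean value gives the rate among patients with known status, and so inherits any selection in that group.
- The patient is left out for want of a recorded outcome. In-hospital deaths always have a record, so they would be over-represented among those analysed, and the rate could be too high instead of too low.

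The article does not say which applies to mortality.

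**3. How large could the undercount be?** Assumptions, none from the article: constant hazard (at low mortality, deaths spread evenly over the 30 days), 30 days counted from admission, a stay of L days, every in-hospital death recorded, and a share c of post-discharge deaths reaching the trial record.

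Share recorded = L/30 + (1 − L/30) × c

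For L = 10 and c = 0.5: 0.333 + 0.667 × 0.5 = 0.667.

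| Stay L (days) | c = 0 | c = 0.5 | c = 1 |
|---|---|---|---|
| 7 | 23% | 62% | 100% |
| 10 | 33% | 67% | 100% |
| 14 | 47% | 73% | 100% |
| 21 | 70% | 85% | 100% |

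**4. In patients.** Assume a true 30-day mortality of 3% among 1990 patients: 1990 × 0.03 = 59.7 deaths. With a 10-day stay:

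- c = 0: 59.7 × 1/3 = 19.9 recorded, 39.8 missed.
- c = 0.5: 59.7 × 2/3 = 39.8 recorded, 19.9 missed.
- c = 1: none missed.

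If missed deaths are counted as alive, the reported rate is 1.0%, 2.0% or 3.0%.

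**5. Between measures.** A biased comparison would need capture, or length of stay, to differ between the five measures. The article gives neither by measure. Every ward is to run all five measures, which largely balances differences in stay between wards.

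**The case against.** The strongest reply is that follow-up to 30 days after discharge is stated in the sentence right after the source. As written, patients are followed past discharge, and how they are contacted is a detail that an article commonly leaves to the full protocol. The case report form, and the assessment schedule in Fig. 3, were not available in the text reviewed and may already provide for vital status. The article also does not describe what the hospital information system holds; follow-up contacts or outside deaths may be entered in it. Adverse events are recorded and judged separately, so mortality is not the only safety information.

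Much of this stands. A reader might infer that the system cannot show deaths outside the hospital, that such deaths are scored as survival, and that the reported figure will be close to in-hospital mortality. The article supports none of these as fact. The system's reach is not described, post-discharge follow-up is planned, and patients of unknown status might be left out instead of counted alive. The near-in-hospital figure needs c = 0, which is one end of the range.

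What the reply does not remove is the text itself. It names one source for the outcome in two sections, it does not connect the stated follow-up to vital status, and its general fill-in rule makes no exception for death.

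**Conclusion.** The point holds as a risk of under-ascertainment, not as a demonstrated bias. On the literal text, deaths outside the hospital can be missed and unknown status can become survival.

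The size cannot be determined from the article. Under the assumptions above, the result runs from a loss of about two thirds of 30-day deaths to no loss at all, depending on a capture rate that is not given. A reader might also infer a distorted comparison between measures if lengths of stay differ; nothing in the article shows such a difference, and the crossover works against differences that come from the wards.

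The primary VTE outcome is not affected. Correction is worthwhile because it is cheap and because an undercounted death rate is easily misread as reassurance on safety.

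**What to change.** First establish what was done. Recruitment began in December 2019 and was expected to complete in December 2023, so for most participants the post-discharge contact has either been made or not.

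If it was made:

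- In Data collection, limit the hospital information system to in-hospital data (operative blood loss and in-hospital events). State that 30-day vital status comes from the patient or family at the follow-up 30 days after discharge, entered on the case report form as alive, dead (with date) or unknown.
- In Handling of missing data, exempt mortality from the fill-in rule, and state that an absent hospital entry is not evidence of survival.
- Report the number of patients with unknown status for each of the five measures.

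If it was not made, name the outcome in-hospital mortality in Hypothesis and outcomes, Data collection and Secondary analysis, and do not report it as 30-day mortality.

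The cost is a form field and a short contact at a follow-up point already stated. The fallback costs a change of name and a narrower claim.
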